#### Inclusion criteria

The inclusion criteria for women are being Iranian, residing in Tabriz, and being at least 18 years old with normal mental or physical status and primiparous who gave birth to a singleton full term neonate.

#### Exclusion criteria

The exclusion criteria for women are having mental disability; being deaf or mute; taking any antidepressant medication e.g. tricyclic antidepressants, serotonin reuptake inhibitors, monoamine oxidase, serotonin-norepinephrine reuptake inhibitor; having stressful incidents during the last 3 months such as divorce, death of first-degree family members, diagnosis of a hard-to-treat or incurable disease of a family member; multiple pregnancy; preterm delivery (less than 37 weeks of gestation); post-term delivery (over 42 weeks of gestation); non-cephalic presentation; emergency cesarean section; history of depression or postpartum depression; obstetric problems such as placenta previa, placental abruption, preeclampsia, neonatal with major malformations, and death of the newborn. Furthermore, if the participants become exposed to any stressful incident during the study, they will be excluded from the study.

#### Scales and data collection

Quantitative data are collected using sociodemographic and obstetric characteristics questionnaires, CEQ 2.0 and SCIB by a research staff member and collected in person. Sociodemographic and obstetric questionnaires will include questions on age, spouse’s age, and medical interventions during labor such as induction and augmentation, epidural analgesia, immobilization in labor.

The second version of CEQ contained 23 items and measures the women’s perceptions of first labour and birth, and includes the following subscales: own capacity (personal feeling about childbirth and labor pain), professional support (information and midwifery care), perceived safety (sense of safety and childbirth memories), and participation (the person’s ability to change childbirth situation). The CEQ consists of 20 items in the form of multiple-choice questions and three items completed using Visual Analog Scale (VAS). Participants will be asked to rate their level of agreement or disagreement with each item by using a 4 point Likert scale where 1 = totally agree; 2 = mostly agree; 3 = mostly disagree; and 4 = totally disagree. Questions answered in the VAS form will be changed from a 0–100 score to 1–4 score where scores 0–40 = score 1, scores 41–60 = score 2, scores 61–80 = score 3, and scores 81–100 = score 4. Statements with negative concepts (experiencing severe pain, feeling tired, scared and having a bad memory) are scored in reverse. Higher mean scores reflect more positive childbirth experiences. The overall Cronbach’s alpha of the original CEQ has not been reported. However, the Cronbach’s alpha for own capacity, participation, perceived safety, and professional support subscales has been reported 0.82, 0.62, 0.78, and 0.88 respectively [34]. This tool will be completed at least 1 month after childbirth.

SCIB contains 33 items and its subscales include internal control, external control, and support. The internal control contains 10 items that focus on the emotions, behavior, pain, and physical functioning (e.g. “I overcame my pain”). The external control contains 11 items that focus on pain relief, information, environment, decisions and procedures, and birth outcome (e.g. “I had control over when procedures happened”). The support contains 12 items that focus on coping methods, staff attitude, empathy and understanding, encouragement, listening, informational support, and support with pain relief (e.g. “The staff dismissed things I said to them”). Questions are scored on a 5-point Likert scale from agree completely to disagree completely. A score of 1 shows less control and support, and a score of 5 shows more control and support. Ten items are scored in reverse. SCIB will be completed 1 month after childbirth. The overall Cronbach’s alpha of the original SCIB has been reported 0.95. Also, the Cronbach’s alpha for internal control, external control, and support subscales has been reported 0.86, 0.93, and 0.93 respectively [21].

Due to the fact that the CEQ 2.0 and SCIB have not been validated in Iran, they will be standardized and validated prior to the start of the main study. The scales will be translated into Farsi using the Forward & Backward Translation method. The translated versions will be edited by two experts in concepts and the final versions will be created. For quantitative valuation of face validity, 20 postpartum mothers will complete the face validity checklist and will be asked to comment on clarity, simplicity, and relevance of items. Based on these notes, the translated items will be revised. The mothers will also be requested to comment on the impact score of the items on a 4-point Likert scale. To obtain the impact score, the percentage of mothers who score the items a value of 4 will be multiplied by the mean total impact score. Impact scores greater than 1.5 will be considered satisfactory [35].

To measure content validity, 10 experts in obstetrics and gynecology, midwifery, psychology, nursing, health promotion and reproductive health, will be invited to comment on transparency, relevance and simplicity of items (CVI = Content Validity Index) and the necessity of items (CVR = Content Validity Ratio). Responses will be scored based on the 4-point Likert scale [“inappropriate” (1); “need to revise” (2); “appropriate but need to modify” (3); and “completely appropriate” (4)]. A CVI greater than 0.79 and CVR greater than 0.62 will be considered satisfactory [36].

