#### Data analysis

The data obtained in the first section of phase one will be analyzed using SPSS Statistics Version 25.0 for Windows (IBM Inc., Armonk, NY, USA). In the cross sectional stage, descriptive statistics will be used to describe the socio-demographic, antenatal and intrapartum factors and childbirth experience. The analytical statistics including univariate will be used to test the correlation between socio-demographic, antenatal and intrapartum variables with the childbirth experience. Then, variables with a correlation of *p* < 0.1 in the univariate analysis will be entered into the multivariable logistic model. All tests will be two-tailed. *P*-value <0.05 will be considered statistically significant. To promote data quality in the cross sectional stage, procedures such as double data entry and range checks for data values will be conducted.

The data obtained in the second section of phase one will be analyzed using SPSS Statistics Version 25.0 for Windows (IBM Inc., Armonk, NY, USA) and AMOS software. Construct validity will be measured using exploratory factor analysis and confirmatory factor analysis. In exploratory factor analysis, the Principal Axis Factoring method and oblimin rotation will be used to extract and rotate the factors. If the items loading are lower than 0.3, the item may be removed [37]. Next, exploratory analysis, confirmatory factor analysis will be used to support the findings of the scale dimensions. Indicators with acceptable values for the model to be approved include Root Mean Square Error of Approximation (RMSEA) < 0.08, Goodness of Fit Index (GFI), Comparative Fit Index (CFI) ≥ 0.90, and Normed chi-square ( x^2^/df < 5). Internal consistency will be assessed using the Cronbach’s Coefficient alpha. The test-retest reliability will be calculated through test-retest of 20 primiparous mothers with a 2 week interval and the calculation of Intra Correlation Coefficient (ICC).

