#### Sample size and sampling method

Purposeful sampling will be used in phase two. The participants in this phase will be selected based on the mean total score of childbirth experience, which is collected in phase one of the study. Women with 10% upper and lower scores of childbirth experience will be selected as the extreme cases. We will seek to interview women with either a positive or negative childbirth experience to collect more comprehensive information about their childbirth experience and its effective factors.

The analysis process will be initiated from the first interview. The aim is to clarify the details and relationships between the pivotal concepts and categories derived from investigating the initial data. In this way, the selection of the participants will continue until the relationships between research concepts and variables, i.e. theoretical saturation, are determined [38]. In this study, the sampling will continue until the researcher felt no further information will be collected during data analysis and coding. Nevertheless, some references estimated 12 participants as the minimum number of participants required for a qualitative study [39].

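### As written, the CEQ 2.0 Likert coding makes higher scores mean a worse childbirth experience, which contradicts the stated interpretation of the score

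*Protocol article*

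**What the plan says.** All the scoring rules for the CEQ 2.0 stand in one paragraph of the protocol article, Phase one, Scales and data collection. The instrument has 23 items: 20 Likert items and three VAS items.

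- Likert codes: "where 1 = totally agree; 2 = mostly agree; 3 = mostly disagree; and 4 = totally disagree".
- VAS recode from 0–100: "scores 0–40 = score 1, scores 41–60 = score 2, scores 61–80 = score 3, and scores 81–100 = score 4". The paragraph does not say what 0 and 100 stand for, or which three items are VAS items.
- Reversal: "Statements with negative concepts (experiencing severe pain, feeling tired, scared and having a bad memory) are scored in reverse". No other items are reversed.
- Interpretation: "Higher mean scores reflect more positive childbirth experiences".

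The score is then used in two places. Phase one, Data analysis, uses univariate analysis to "test the correlation between socio-demographic, antenatal and intrapartum variables with the childbirth experience", followed by a multivariable logistic model. Phase two, Sample size and sampling method, uses the total score to choose interviewees: "Women with 10% upper and lower scores of childbirth experience will be selected as the extreme cases". That section describes them as women with a positive or a negative experience. No other part of the article restates or corrects the key.

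**The concern.** With agreement coded low, a positive statement gives its lowest score to the most satisfied woman. Reversing the negative statements then brings them into line with the positive ones, but in the wrong direction: both kinds now score high when the experience is bad. The sentence on interpretation says the opposite.

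The CEQ 2.0 mean is the study's main outcome. If the key were applied as printed and the result read as the interpretation sentence directs, a factor that improves the experience would appear to worsen it, and the reverse. The women presented to phase two as positive cases would be the negative ones. The integrated findings go to the Delphi panel as recommendations, so an unnoticed sign error could reach the guideline.

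**Working it through.** **Inputs** (all from Scales and data collection): 20 Likert items coded 1 to 4 as quoted; reversal of negative statements only, which on a 1–4 scale is 5 − x; three VAS items recoded 1 to 4, rising with the raw score; stated direction, higher = more positive.

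**Step 1: the key applied item by item**

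| Statement | Experience | Answer | Code | After reversal rule |
|---|---|---|---|---|
| Positive | best | totally agree | 1 | 1 |
| Positive | worst | totally disagree | 4 | 4 |
| Negative | best | totally disagree | 4 | 5 − 4 = 1 |
| Negative | worst | totally agree | 1 | 5 − 1 = 4 |

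Every favourable answer ends at 1 and every unfavourable one at 4. The stated direction is therefore not reproduced for any Likert item.

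**Step 2: the 23-item mean.** The VAS anchors are not given, so both extremes are shown.

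- VAS high = favourable after any reversal: best (20×1 + 3×4)/23 = 32/23 = 1.39; worst (20×4 + 3×1)/23 = 83/23 = 3.61.
- VAS high = unfavourable: best 23/23 = 1.00; worst 92/23 = 4.00.

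Under either reading a higher mean is a worse experience. A mixture of VAS directions falls between the two.

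**Step 3: the key consistent with the stated interpretation.** With 4 = totally agree, negative statements reversed, and VAS items oriented so that 4 is favourable, best = 92/23 = 4.00 and worst = 23/23 = 1.00. Keeping the printed codes and reversing the positive statements instead gives the same result.

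**Step 4: size of the inversion if the VAS items run the favourable way.** This is a one-factor simulation with 200,000 women, 20 Likert and 3 VAS items. The equal loadings and the cut-points are assumptions. The literal total is compared with the consistently keyed total.

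| Assumed loading | Correlation, literal vs consistent total | Share of literal upper 10% in true lowest 10% | In true upper 10% |
|---|---|---|---|
| 0.4 | −0.92 | 69% | 0% |
| 0.5 | −0.95 | 74% | 0% |
| 0.7 | −0.98 | 82% | 0% |

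Here true means ranked on the consistent total. At every loading, all women in the literal upper 10% were below the median of that total. If the VAS items also ran the unfavourable way, the literal total would be an exact mirror image (correlation −1).

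**Step 5: Cronbach's alpha, on the same VAS assumption.** Take a common inter-item correlation of 0.32 (assumed). For 23 items keyed alike, alpha = 23×0.32/(1 + 22×0.32) = 7.36/8.04 = 0.92. With three items opposed, 3×20 = 60 of the 253 item pairs change sign. The mean correlation becomes 0.32×(253 − 120)/253 = 0.168, and alpha = 23×0.168/(1 + 22×0.168) = 3.87/4.70 = 0.82.

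**The case against.** The strongest reply is that this is a slip in a condensed article. The intended direction is stated outright, the CEQ is an established instrument, and the raw answers can be re-keyed at any time. That is fair on how recoverable the error is, but it does not remove the contradiction. The article gives the codes, the reversal rule and the interpretation in full, so this is not detail left to a longer document. Reading 1 to 4 as raw form codes does not help either, because the rule then reverses the wrong set of items.

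Several stronger inferences are tempting, and the document does not support them.

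- **That the factor analyses would be damaged.** Reflecting an item changes the sign of its correlations only. The absolute size of its loading and the confirmatory fit indices (RMSEA, GFI, CFI, chi-square/df) do not change.
- **That the VAS items certainly conflict with the Likert items.** This depends on anchors that are not stated. The overall alpha in the working is conditional on it. No subscale alpha can be worked out, because the article does not say how many CEQ items each subscale has or where the VAS items sit.
- **That the SCIB has the same error.** Its anchors are described as "Questions are scored on a 5-point Likert scale from agree completely to disagree completely", with no numbers attached. The stated direction (5 = more control and support, ten items reversed) is coherent if agreement is coded 5, so there is no contradiction there.
- **That every association would be reversed.** The sign flips for factors that are themselves correctly coded. If the SCIB happened to be miscoded in the same way, the CEQ–SCIB association would keep its correct sign.
- **That phase two would interview the wrong women.** Both tails are taken, so largely the same women are chosen with their labels exchanged. An in-depth interview would probably expose a swapped label.

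**Conclusion.** The point holds in this form: the Likert codes, the reversal rule and the interpretation sentence are mutually inconsistent, and following the first two inverts the main outcome. The inversion of the 20 Likert items is a deduction from the text and needs no assumption. The inversion of the 23-item mean holds under either VAS reading (best 1.00 to 1.39, worst 3.61 to 4.00).

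Two consequences follow if the key is applied literally: associations with correctly coded factors change sign, and the upper and lower 10% in phase two carry the wrong labels. A drop in overall alpha, from about 0.92 to 0.82 in the illustration, is conditional on high VAS scores being favourable and on the assumed inter-item correlation. The simulated correlations of −0.92 to −0.98 rest on the same VAS assumption and on assumed loadings of 0.4 to 0.7.

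The article does not show which key will be used in the data file, so the harm is a risk of literal application and not an established error in results. It should be corrected before any scoring, because the direction of the main outcome depends on it.

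**What to change.** Reconcile the three sentences in Scales and data collection:

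- Code positive statements 4 = totally agree to 1 = totally disagree, with negative statements reversed. Alternatively, keep the printed codes and reverse the positive statements instead of the negative ones.
- State the VAS anchors, and orient the three VAS items so that 4 is the more positive answer.
- Before any analysis, check that every item-total correlation is positive. An item with a negative value should be checked for its key before any decision to drop it.

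The cost is a rewording of the key and one routine check in the scoring program. No new data, change of sample size or change of design is needed.

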#### Data analysis

The data obtained in the first section of phase one will be analyzed using SPSS Statistics Version 25.0 for Windows (IBM Inc., Armonk, NY, USA). In the cross sectional stage, descriptive statistics will be used to describe the socio-demographic, antenatal and intrapartum factors and childbirth experience. The analytical statistics including univariate will be used to test the correlation between socio-demographic, antenatal and intrapartum variables with the childbirth experience. Then, variables with a correlation of *p* < 0.1 in the univariate analysis will be entered into the multivariable logistic model. All tests will be two-tailed. *P*-value <0.05 will be considered statistically significant. To promote data quality in the cross sectional stage, procedures such as double data entry and range checks for data values will be conducted.

The data obtained in the second section of phase one will be analyzed using SPSS Statistics Version 25.0 for Windows (IBM Inc., Armonk, NY, USA) and AMOS software. Construct validity will be measured using exploratory factor analysis and confirmatory factor analysis. In exploratory factor analysis, the Principal Axis Factoring method and oblimin rotation will be used to extract and rotate the factors. If the items loading are lower than 0.3, the item may be removed [37]. Next, exploratory analysis, confirmatory factor analysis will be used to support the findings of the scale dimensions. Indicators with acceptable values for the model to be approved include Root Mean Square Error of Approximation (RMSEA) < 0.08, Goodness of Fit Index (GFI), Comparative Fit Index (CFI) ≥ 0.90, and Normed chi-square ( x^2^/df < 5). Internal consistency will be assessed using the Cronbach’s Coefficient alpha. The test-retest reliability will be calculated through test-retest of 20 primiparous mothers with a 2 week interval and the calculation of Intra Correlation Coefficient (ICC).

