#### Sample size and sampling method

According to Nunnally & Bernstien, for a factor analysis in the validation of scales, 10 samples per item are required [31]. Given the 33 items in SCIB, 330 samples are needed. However, a sample of 660 people is required due to the sampling plan and the design effect of 2. Considering that the sampling plan in the first phase is cluster, the design effect must be considered. “The loss of effectiveness by the use of cluster sampling, instead of simple random sampling, is the design effect” [28]. Using a cluster sample usually needs a larger sample size than a simple random sampling and for a well-designed study, the design effect usually ranges from 1 to 3 [32, 33]. Considering a minimum 20% attrition rate, the total required sample size is calculated to be a minimum of 800 participants.

First, the rate of vaginal childbirth in public and private hospitals will be extracted separately. Then, all of the urban and suburban Tabriz health centers will be listed and numbered (114 centers). Using cluster sampling and the website www.random.org, approximately half of the centers will be randomly selected. A list of potential participants will be arranged based on the health records at each selected center. From the list, the required sample size for each center will be determined using the proportional sampling method by the rate of vaginal childbirth in public and private hospitals and the samples will be randomly selected. Using the phone number registered in each record, the researcher will call the potential participants and invite them to participate in the study.

The eligible participants will be provided with full explanations about the study objectives and procedures. Socio-demographic questionnaire, Childbirth Experience Questionnaire 2.0 (CEQ 2.0), and Support and Control in Birth questionnaire (SCIB) will be filled out in a relatively quiet environment by a research staff member and collected in person. A number of participants are likely to be illiterate, so the questionnaires will be completed by the researcher in order for the data collection method to be the same for all individuals. Obstetrics information will be collected by referring to individuals’ medical records. Also, informed consent will be obtained before collecting information from women’s medical records.

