## Discussion

The childbirth process is described as a complex, multidimensional and individual experience with important outcomes of a safe birth and gaining favorable experiences during labor and birth. However, psychological outcomes that women experience are frequently ignored [1, 45] which may have a negative impact on women’s attitudes towards vaginal birth; and it may influence their personal life in the future. The present study will provide detailed information on the experiences of a large group of Iranian primiparous women and the factors that are associated with the experiences.

The proposed study has a few strengths. It will fill crucial knowledge gaps in supporting women during childbirth in an Iranian context. Therefore, it is expected to have important clinical implications. The development of an evidence-based multi-method guideline can be used as a starting point for the development of a guideline for maternity care. It is also designed with a mixed method approach; therefore, it supports the integration of different, even contradictory approaches and methods to understand the concepts [29, 30]. Quantitative and qualitative data collection will assist us in bettering our understanding of women’s experiences during childbirth.

This is among a few studies into the childbirth experience that not only explained women’s experience but also will collect expert opinions. In addition to the development of guidelines based on women’s experience and preferences, the method will engage the experts in the process of guideline development and will investigate the feasibility and cost-effectiveness of the recommendations within Iranian culture.

In addition to teaching hospitals, women admitted to private hospitals will be also included in the current study. In Iran, care conditions and protocols depend on the hospital. As a result, the inclusion of patients admitted to both public and private hospitals can produce more accurate and comprehensive results. Assuming that lifestyle and social environments may affect the expectations and preferences of women and their perception of the childbirth experience, women from health centres in both urban and suburban areas will be included.

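### Phase one samples women by health centre and doubles the sample for it, but the stated analysis makes no allowance for centre

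*Protocol article*

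**What the plan says.** The phase one section on sample size and sampling method starts from a rule for scale validation: "for a factor analysis in the validation of scales, 10 samples per item are required". It continues: "Given the 33 items in SCIB, 330 samples are needed". It then turns to the sampling: "Considering that the sampling plan in the first phase is cluster, the design effect must be considered". The consequence is that "a sample of 660 people is required due to the sampling plan and the design effect of 2", with the remark that "for a well-designed study, the design effect usually ranges from 1 to 3". The last step is attrition: "Considering a minimum 20% attrition rate, the total required sample size is calculated to be a minimum of 800 participants". The clusters are health centres. About half of the 114 in the city are drawn at random, and women are then drawn at random from the records of each selected centre.

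The phase one Data analysis section describes the cross-sectional analysis: "The analytical statistics including univariate will be used to test the correlation between socio-demographic, antenatal and intrapartum variables with the childbirth experience". Variables with p<0.1 go into a multivariable logistic model. Tests are two-sided at 0.05, and the software is SPSS 25. Neither this section nor any other names a random centre effect, GEE, cluster-robust variance or a complex-samples procedure. The section mentions p-values but no confidence intervals.

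The Discussion adds a remark on care: "In Iran, care conditions and protocols depend on the hospital".

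**The concern.** The protocol itself says that clustering costs information and sizes the study for a doubling of variance. That cost must also enter the standard errors. If 660 women carry the information of 330, an analysis that counts them as 660 independent observations overstates its precision whatever the sample size.

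Two kinds of result are exposed. One is the mean childbirth experience score, which is an objective of phase one. The other is the set of associations with socio-demographic, antenatal and intrapartum factors and with perceived support and control. Factors that differ between centres would pass the p<0.1 screen and reach p<0.05 too often. Phase three integrates the phase one findings with the qualitative results and gives them to the Delphi experts as recommendations.

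**Working it through.** **Inputs from the protocol:** 33 items, 10 women per item, design effect (DEFF) 2 with a usual range of 1 to 3, 20% attrition, total 800, about half of 114 centres, two-sided 0.05, screen at 0.10. **Assumed:** 57 centres, since the exact number is not given.

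**1. The protocol's sample size.** 33 × 10 = 330, and 330 × 2 = 660. Then 660 × 1.2 = 792, which rounds to the stated 800. So the design effect enters here, as a multiplier on the factor-analysis sample size. At DEFF 2, 660 women carry the information of 660 / 2 = 330.

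**2. ICC implied by DEFF 2.** ICC = (DEFF − 1)/(m − 1), with m women per centre.
- 640 women (800 less 20%): m = 640/57 = 11.2, ICC = 0.098
- 660 women: m = 11.6, ICC = 0.095
- 800 women: m = 14.0, ICC = 0.077

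**3. Mean score, or a factor constant within a centre.** True SE = naive SE × √DEFF. Actual type I error of a nominal two-sided test = 2 × [1 − Φ(z/√DEFF)], with z = 1.960 for the 5% test and 1.645 for the 10% screen. At DEFF 2: 1.960/1.414 = 1.386, which gives 16.6%.

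| DEFF | SE ratio | 5% test | 10% screen |
|---|---|---|---|
| 1 | 1.00 | 5.0% | 10.0% |
| 1.5 | 1.22 | 11.0% | 17.9% |
| 2 | 1.41 | 16.6% | 24.5% |
| 3 | 1.73 | 25.8% | 34.2% |

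These figures depend only on the design effect, not on the assumed 57 centres.

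**4. Woman-level factors.** The design effect for an association is about 1 + (m − 1) × ICC of the factor × ICC of the outcome. When the outcome has DEFF 2, (m − 1) × ICC of the outcome = 1, so this reduces to 1 + ICC of the factor. The simulation used 57 centres of 12 women, a normally distributed outcome, an ordinary correlation test and 4,000 runs.

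| ICC of factor | DEFF | 5% test, formula | 5% test, simulated |
|---|---|---|---|
| 0 | 1.00 | 5.0% | 5.6% |
| 0.1 | 1.10 | 6.2% | 6.2% |
| 0.25 | 1.25 | 8.0% | 8.6% |
| 1 (constant within centre) | 2.00 | 16.6% | 17.8% |

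A smaller simulation (57 centres of 11, 600 runs) gave 5.3%, 10.2% and 14.3% at factor ICCs of 0, 0.3 and 1. The last has a Monte Carlo error of √(0.143 × 0.857/600) = 1.4 percentage points, so it is compatible with 16.6%. Cluster-robust standard errors on the same data gave 5.5%, 6.3% and 4.8%, close to nominal.

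**The case against.** **The protocol never says that women are independent.** That is true. This is a condensed article, the analysis plan is not shown, and variance estimation is often left to that plan. But the Data analysis section is specific: it fixes the software, the screen, the model, the sidedness and the significance level. The sampling section makes clustering an explicit requirement. What stands is that the requirement is not carried into the stated analysis. A deliberate decision to assume independence cannot be shown.

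**The 17% fits few of the planned tests.** This also stands. The covariates that the protocol names are woman-level: age, spouse's age, induction, augmentation, epidural analgesia, immobilization, and perceived support and control. Urban or suburban location is the clearest centre-level factor, but it is described as a feature of coverage and not listed as a covariate. A reader might infer that all p-values and confidence intervals are badly wrong. The documents do not support that: woman-level tests may be nearly correct, and no intervals are planned.

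**DEFF 2 is a planning multiplier, not an estimate for this outcome.** Correct, and at the lower end of the protocol's range there is no error. The range is therefore reported with the figure.

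**Hospital clustering.** A reader might infer from the Discussion's remark on care that women who share a hospital form a second set of clusters, with an error that could be stated. The idea is plausible, but hospital is not a sampling stage, and neither the number of hospitals nor a hospital ICC is given. Public or private birth need not be constant within a health centre, so the centre-level figures do not carry over to it.

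**The guideline does not rest on p-values alone.** Phase two selects women by extreme scores, and phase three also uses graded literature, qualitative findings and a Delphi consensus. This limits the consequences. It does not make the phase one inference correct.

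**Conclusion.** The point holds in a limited form. The protocol requires clustering to be considered, pays for it in sample size and then states an analysis with no allowance for it. Followed as written, the analysis understates the standard error of the mean score, and of any factor constant within a centre, by a factor of 1.41 at the protocol's own design effect. A nominal 5% test of such a factor then has about 17% type I error (5% to 26% over design effects of 1 to 3), and the p<0.1 screen about 24%. For woman-level factors the 5% test runs at about 5% with no clustering of the factor, 6% at a covariate ICC of 0.1, and 8–10% at 0.25–0.3.

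These sizes assume that the planning design effect applies to the childbirth experience score. The implied ICC of 0.08 to 0.10 is back-calculated on 57 centres and is not documented. The simulations used a continuous outcome, so for the logistic model they are a guide only. Any effect of shared birth hospital remains unquantified.

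**What to change.** In the phase one Data analysis section, state that:

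- means and proportions are estimated with health centre as the primary sampling unit, for example with SPSS Complex Samples;
- every univariate screening test and the multivariable model use a cluster-adjusted method with health centre as the cluster (a mixed model, GEE or cluster-robust standard errors);
- the observed ICC of the childbirth experience score is reported.

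Examine birth hospital in a sensitivity analysis, for example with a random hospital intercept if there are enough hospitals. A hospital fixed effect is not suitable, because it would absorb the public/private contrast.

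The cost is a change of wording and somewhat wider uncertainty. No further women are needed. The centre is known from the sampling, so it only has to be kept as a variable in the data set.
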